## Assignment of interventions: blinding

### Who will be blinded {17a}

Participants will be blinded regarding the objective of the TSST and the relaxation exercise variations. At no time, participants will be aware that there are two relaxation exercises and that they may be in the control group. Participants will know from the recruitment that there is a virtual and a natural setting but are not aware of the composition of the setting.

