### Implementation {16c}

Participants will be registered after they have voluntarily contacted the study management and the inclusion and exclusion criteria have been checked. After completion of T0, study personnel will perform group assignment. For this purpose, the study personnel enters the group number of 4 groups into the pseudo random number generator, which then generates the allocation sequence and assigns the participants to the conditions.

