### Methods in analysis to handle protocol non-adherence and any statistical methods to handle missing data {20c}

If data is missing, a distinction will be made between data missing at random and missing not at random by computing a Missing Completely At Random (MCAR) test. For data missing at random (e.g., contaminated saliva samples), multiple imputation and maximum likelihood estimation can be used [55]. Completely missing data (e.g., due to failure of technical components) will be excluded. The handling of missing data in questionnaires will depend on the recommendations in the respective manual. Outliers (e.g., due non-adherence) will also be analyzed and excluded if necessary.

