## Oversight and monitoring

### Composition of the coordinating center and trial steering committee {5d}

The study will be a single-center study. Responsible and involved persons will be staff members of the Clinic of Child and Adolescent Psychiatry, Psychosomatics, and Psychotherapy. The responsibility will exclusively lie with the study management. No other persons will be involved.

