### Adverse event reporting and harms {22}

Adverse events could occur in this study, particularly during AA and stress induction. Since the AA will be conducted via smartphones, technical errors cannot be excluded. Any problems that occur during the AA will be queried using the app itself (e.g., “Were there any technical problems with the app?”), and queried again at T2 and noted on a protocol. If the input will not work or the reminders of the app will be missing completely, the AA can be repeated. For this purpose, participants can contact the study management.

During stress induction in VR, VR sickness can occur despite precautions. Should a break be necessary, this will be noted in detail to document a shift in the schedule. Depending on the extent of the disturbance, the data will be excluded from the evaluation.

If the stress induction is too stressful and not bearable for the participant, the TSST will be interrupted. Experience shows that this is very unlikely. In general, the survey could be perceived as burdensome by children and adolescents. If this becomes too stressful for the participants, breaks can be taken or in extreme cases the investigation can be aborted. However, this will also lead to exclusion from the study. All adverse effects (e.g., high stress levels and VR sickness) are noted in detail on a protocol.

In summary, possible deviations from the planned procedure will always be collected and reported.

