The following potential limitations or challenges may arise in the three main areas of the study: Regarding stress induction, not all parameters in both groups may respond to the induction with equal strength. Firstly, non-responders are part of everyday life in stress research [59], and secondly, a stress response is not always evident at all levels. Therefore, a multimodal psychometric and biological measurement is provided [58]. Based on this, more reliable statements about the stress response can be made. Possible influences of sex or age on the various stress parameters are addressed by the inclusion and exclusion criteria and randomization across groups. A potential influence of the VR environment itself on the stress level in children and adolescents has not yet been investigated. Factors such as VR sickness and presence could have an influence and will therefore be documented in this study. During the AA, no control of the collection of data (e.g., saliva samples and subjective data) will be feasible, but will be compensated as much as possible by the use of a medication event monitoring system, previous demonstration of saliva sample collection and app use, notifications via the app in clear time limits, and reward bonuses. Technical problems cannot be completely excluded, but in such cases it is possible to contact the study personnel in order to minimize data loss. During the relaxation exercise, there will be no recording of whether the breathing exercise is performed correctly in the HCE and whether the NR really does not include any breathing exercise. However, the presence of the experimenter is believed to have a positive effect on the correct execution according to the instructions.

In summary, this study aims to improve the understanding of the mental and physiological effects of acute and everyday stress and the applicability of a virtual stress paradigm to investigate acute stress and the stress-reducing effect of an HCE in children and adolescents. Findings of this study may facilitate future stress research in the field of children and adolescents and may lead to an expanding use of these laboratory stressors paradigms in clinical and population-based trials.

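### Only participants are blinded, and nothing masks the HCE/NR arm while discretionary outlier exclusions are decided on primary data

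*Protocol article*

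**What the plan says.** Under Who will be blinded {17a} the protocol article names one group: "Participants will be blinded regarding the objective of the TSST and the relaxation exercise variations". It adds that participants do not know a second relaxation exercise exists. Experimenters, data handlers and analysts are not mentioned.

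Three places show that staff know the relaxation arm:
- Implementation {16c}: "After completion of T0, study personnel will perform group assignment".
- The Discussion concedes that correct performance of the exercise is not recorded, and relies on staff instead: "the presence of the experimenter is believed to have a positive effect on the correct execution according to the instructions".
- The coordinating-centre item {5d}: "The responsibility will exclusively lie with the study management".

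The discretion lies in the section on non-adherence and missing data {20c}: "Outliers (e.g., due non-adherence) will also be analyzed and excluded if necessary". No threshold is given. Adverse event reporting {22} has a second discretionary rule, for disturbed VR sessions: "Depending on the extent of the disturbance, the data will be excluded from the evaluation".

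Superiority of HCE over NR is a stated expectation (Objectives {7}, Trial design {8}). The outcomes it is tested on are primary (Outcomes {12}).

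**The concern.** An exclusion described only as being made when necessary is a judgement. If the person judging can see both the value and the relaxation arm, the decision can lean, without any intent, towards dropping values that count against HCE. The retained data set is then selected on arm and outcome together, and a later p-value correction does not undo that selection.

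Non-adherence is the document's own example of a reason for exclusion. For the exercise at the second appointment there is no recording of adherence, so such a call would rest on staff impression.

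The arm label is not needed to judge whether a hormone concentration or a mood rating is usable. The exposure is therefore avoidable. It lies in data handling rather than measurement, because outcomes are self-reported by blinded participants or come from sensors and the laboratory.

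**Working it through.** **Inputs from the document.** Total N = 84, f = .30, power 95% (Sample size {14}); α = .05 (Statistical methods {20a}); 8 saliva samples at the second appointment (Intervention description {11a}); four groups from a 2×2 design (Trial design {8}).

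**The plan's own figure.** The sample size reproduces as a two-group, between-factor repeated-measures test with m = 8 measurements. The correlation ρ = 0.5 is an assumption, since the document gives none.

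λ = N·f²·m / [1 + (m − 1)ρ] = 84 × 0.09 × 8 / (1 + 7 × 0.5) = 60.48 / 4.5 = 13.44

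With 1 and 82 degrees of freedom the power is 0.952, and 84 is the smallest N that reaches 95%. With m = 7 the answer is 85, and with m = 9 it is 83. So 84 fits a comparison of two halves of the sample, 84 / 2 = 42 HCE versus 42 NR if allocation is even. Even allocation is an assumption, because a simple uniform draw does not guarantee it.

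**Effect of arm-aware exclusion.** The document gives no outlier rate, so this is an illustration. Assumptions: no true HCE effect; 42 per arm; standard normal outcome; pooled t-test at two-sided .05 without multiplicity correction; 20,000 simulated trials. A value may be dropped only if it lies beyond 2 SD and counts against HCE (unfavourable in the HCE arm, or favourable in the NR arm). The most extreme are dropped first, up to a cap.

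| Handling | False result in favour of HCE | Either direction | Mean bias towards HCE (SD) |
|---|---|---|---|
| No exclusion | 2.5% | 4.8% | 0.00 |
| Arm-aware, at most 1 value | 4.4% | 6.0% | 0.05 |
| Arm-aware, at most 2 values | 6.0% | 6.9% | 0.08 |
| Arm-aware, at most 4 values | 6.9% | 7.7% | 0.11 |
| Symmetric 2 SD cut-off, arm ignored | 2.6% | 5.2% | 0.00 |

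Simulation error is about √(0.025 × 0.975 / 20,000) = 0.1 percentage point at the null rate. The increase flattens because few values qualify: the expected number is 84 × 0.0228 ≈ 1.9 per trial.

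**Sensitivity to the selection assumed.**
- Dropping the k least favourable values from each arm, outliers or not (40,000 trials): 2.4%, 8.2%, 17.7% and 30.3% for k = 0, 1, 2, 3. Of the values this removes from the HCE arm, only 62%, 44% and 32% lie beyond 2 SD for k = 1, 2, 3.
- Dropping only the highest one, two or three HCE values, normal data: 4.7%, 7.5%, 10.7%.
- The same with right-skewed data (log-SD 0.6) and a raw-scale t-test: 5.7%, 10.2%, 15.6%. With the Mann-Whitney test that the plan would use for non-normal data: 4.1% and 5.7% for one and two values.

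**The case against.** The strongest objection is that the central fact is inferred. No section says who decides exclusions or that this person sees the arm, and masking during data cleaning may be set out in an analysis plan that is not shown. This stands in part: the point is a route left open, not evidence that it is used. But the blinding item is answered, and the answer names participants only.

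A reader might take "No other persons will be involved" to mean that no outsider touches the data. The sentence sits under study responsibility, and it cannot be literal, because an external laboratory assays the saliva under participant code ({26b}, {27}). Nothing gives that laboratory the exclusion decision.

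A reader might also count the disturbed-session rule in {22} as a second route to a biased HCE result. It concerns VR sickness during the stress test, before the relaxation exercise, so it bears mainly on TSST-VR versus TSST-IV and is only secondary support here. Nor do ECG and gaze processing add much. Data management {19} says heart-rate data are transmitted without processing, and the gaze targets are the panel and camera, viewed before relaxation begins.

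Some safeguards exist. Samples carry only the participant code, and saliva is kept six months so that outlying concentrations can be checked. At least 30% of the questionnaire, mood and gaze data are double coded, and deviations are to be reported. These reduce the risk but do not close it: a re-assay can confirm a value without settling whether it stays in, and the double coding is not described as masked.

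Finally, a fixed symmetric cut-off would remove the bias without masking, as the table shows. That is correct for numerical outliers. It would not cover exclusions for non-adherence, which rest on judgement.

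**Conclusion.** The concern holds as a cheap improvement. The document masks the relaxation arm from participants only, staff assign and observe that arm, and outliers on primary outcomes may be dropped at discretion. Exclusions can therefore be made with the HCE/NR arm known. This is an inference from those sections, not a statement in any of them.

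On realistic assumptions the false HCE-superiority rate rises from about 2.5% to about 4–7%, with a bias of 0.05 to 0.11 SD. This rests on no true effect, 42 per arm, normal data, candidates beyond 2 SD and a single uncorrected test. How far the planned false discovery rate correction across all primary outcomes would change these rates was not computed.

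A reader might infer from the 8–30% figures that a few routine exclusions could readily manufacture an HCE effect. The document does not support that reading. Those figures need opposite-direction trimming of both arms regardless of whether the values are outliers, which is a deliberate worst case rather than outlier handling.

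**What to change.** In {17a} and {20c} of the protocol article, state that:
1. the HCE/NR label is withheld from the working data set while outlier and non-adherence exclusions are decided;
2. the exclusion list is dated and locked before the label is restored;
3. the HCE versus NR test is reported with and without the excluded values.

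This can still be adopted after recruitment, provided exclusions are not yet final.

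The cost is small. N and power are unchanged, and no visits or assays are added. The data are already pseudonymised and the list linking codes to persons is stored separately. The relaxation code must also be held apart from the working file. Masking is incomplete for staff who ran sessions and remember arms, so an existing team member who did not run the session should make the decisions where possible.

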### Procedure for unblinding if needed {17b}

There are no expected circumstances for unblinding participants during the study.

## Data collection and management

### Plans for assessment and collection of outcomes {18a}

During the short telephone screening, questions will be asked about schooling, employment, illnesses, and medication intake in order to check the inclusion and exclusion criteria.

To measure stress levels, subjective mood will be registered using 10-item Likert scales that cover the emotional components stress / tension, sadness, anxiety / fear, anger, and aggression (e.g., “At the moment I feel stressed, tensed or charged.”). For the psychophysiological measurement of hormone concentrations, heart rate and gaze behavior, salivettes, electrocardiogram / activity sensors (EcgMove 4 by movisens), and eye-tracking systems (Tobii Pro Glasses 2 and Tobii Eye-Tracking built in HTC VIVE Pro Eye Virtual Reality Glasses) will be used.

During the AA, subjective mood ratings and hormone concentrations of cortisol and alpha-amylase will be measured as mentioned above. Subjective sleep quality / quantity and the evaluation of the day will be assessed by means of morning and evening protocols (e.g., “How good and restful was your sleep?” or “How stressful was today overall?”) [27]. The nature and intensity of stressful events in the domains of family, friends, school, and health since the last survey will be registered at several time points followed by questions on used coping strategies (e.g., “I have recovered.” or “I’ve enlisted help from others.”) [28, 29].

The first test part of the Culture Fair Intelligence Test 20-R – Scale 2 (CFT 20-R) [30] will be used to estimate participants’ intelligence. In general, the test consists of two parts (part 1: 56 items, part 2: 45 items) with four sub-tests each (classification, series, analogies, and matrices).

To assess possible behavioral and mental problems, the Mini-International Neuropsychiatric Interview for Children and Adolescents 6.0 (MINI-KID 6.0) [31], the Child Behavior Checklist 6-18 R (CBCL/6-18R) [32], and the Youth Self-Report 11-18 R (YSR/11-18R) [32] will be used. The MINI-KID 6.0 is a structured clinical interview for the assessment of psychiatric disorders with the help of diagnostic sections (A–X) and dichotomous response format (Yes-No). The CBCL/6-18R (answered by parents and legal guardians) and the YSR/11-18R (answered by children and adolescents) enable the analysis of 8 scales (Anxious / Depressed, Withdrawn / Depressed, Aggressive Behavior, Rule-Breaking Behavior, Somatic Complaints, Attention Problems, Social Problems and Thought Problems) and 3 total scores (Total Problems, Internalizing Broad Band and Externalizing Broad Band Score).

The Pubertal Development Scale (PDS) [33] will be collected to assess the puberty status of the participants.

The assessment of temperament (Novelty Seeking, Harm Avoidance, Reward Dependence and Persistence) and character (Self-directedness, Cooperativeness and Self-transcendence) will be done via the Junior Temperament and Character Inventory 12-18 R (JTCI 12-18 R) [34]. The five personality traits Neuroticism, Extraversion, Openness to Experience, Conscientiousness, and Agreeableness will be measured by the 10 items of the 10 Item Big Five Inventory (BFI-10) [35].

The intensity of anxiety and depression will be assessed by the 21 items of the Beck Anxiety Inventory (BAI) [36, 37] and the state and trait scales (20 items each) of the State-Trait-Anxiety-Depression-Inventory (STADI) [38]. Moreover, aggression will be measured by the 29 items, summarized in 4 scales (Anger, Hostility, Physical and Verbal Aggression) of the Aggression Questionnaire (AQ) [39, 40]. The 15 items and 3 scales (Non-planning, Motor and Attentional Impulsivity) of the Barratt Impulsiveness Scale – Short Version (BIS-15) [41, 42] will be used to assess the nature and intensity of impulsive behavior. In addition, to measure 3 empathy domains (Cognitive, Affective, and Somatic) with 2 valence facets (Positive and Negative), the Cognitive, Affective and Somatic Empathy Scales (CASES) [43, 44] are used, which consist of 30 items. Alexithymia as a cluster of emotional processing deficits will also be assessed using the 20 items and 3 dimensions (Difficulties Identifying Emotions, Difficulties Describing Emotions and Externally Oriented Thinking) of the Alexithymia Questionnaire for Children (AQC) [45, 46].

The survey of various traumas in the past (sexual, emotional and physical abuse, emotional, and physical neglect) will be done via the Childhood Trauma Questionnaire (CTQ) [47, 48] consisting of 28 items.

Coping of everyday stressful events will be assessed by the subscales (Problem Solving, Social Support, Avoidant Coping, Palliative Emotion Regulation and Anger-related Emotion Regulation) of the Questionnaire for the Measurement of Stress and Coping in Children and Adolescents 3-8 R (SSKJ 3-8 R) [49].

In the TSST-VR condition, the feeling and experience of being in a virtual environment will be measured by the IGroup Presence Questionnaire (IPQ) [50] consisting of 14 items. Unpleasant physical sensations caused by VR will be registered by the Virtual Reality Sickness Questionnaire (VRSQ) [51] consisting of 9 items.

The questionnaires are sufficiently reliable and therefore constitute standard measures in research and therapy. The values of test-retest reliability range from about .56 to .87 and the internal consistencies range from Cronbach’s alpha = .62 to .95. Furthermore, the studies mentioned above examined the construct and criterion validities of the instruments and showed that they are also sufficiently valid.

### Plans to promote participant retention and complete follow-up {18b}

For motivation, the benefits resulting for the participant will be highlighted, e.g., comprehensive diagnostics, insights into VR or eye-tracking glasses as well as the expense allowance. Especially the AA needs to be strengthened; therefore, a bonus in the expense allowance will be promised for conscientious participation.

No further data will be collected from the participants if participation is discontinued.

### Data management {19}

A double coding of at least 30% of the data (questionnaires, mood ratings, processing of gaze data) is planned. Electronic data (e.g., heart rate and collected data during AA) will be transmitted without processing. The saliva samples will be analyzed once. As a security concept, the data will be stored locally with local backup.

### Confidentiality {27}

Personal information, study data, and the list of assignments between participant code and personal data will be stored separately and locked away. The assignment list will be destroyed 1 year after completion of the study, whereby the participant data will be anonymized. Until then, the data will only be processed pseudonymously under the participant code. During analyses, the saliva samples will be passed on to an external laboratory that is subject to data protection and privacy law. Furthermore, the saliva samples will only be labelled with participant code.

### Plans for collection, laboratory evaluation, and storage of biological specimens for genetic or molecular analysis in this trial/future use {33}

The saliva samples will be collected by the participants themselves during the AA, stored in the refrigerator and brought along for the testing appointment. These and the samples collected during the testing procedures will be stored at −20 °C locally until shipping to the laboratory. After analysis of the hormone concentrations in the external laboratory, the samples will be stored additional 6 months to enable control analyses for outliers. Subsequently, they will be destroyed, and thus, further storage or analysis will not be possible.

## Statistical methods

### Statistical methods for primary and secondary outcomes {20a}

The parameters of the objective stress reactions will include heart rate, gaze behavior, cortisol, and alpha-amylase. For the analysis of the subjective stress reactions, we will use the self-reported mood ratings of the participants. The saliva samples will be determined by an external laboratory to analyze cortisol and alpha-amylase responses. For statistical analysis, we will use the software IBM SPSS Statistics 28 (IBM Corp., Armonk, NY) and R [52]. After checking the normal distribution of the data, parametric or non-parametric tests will be applied accordingly. Possible differences in the responses of cortisol, alpha-amylase, heart rate, gaze behavior, and mood ratings between the groups (between-subject factors: TSST-VR vs. TSST-IV, HCE vs. NR) and over time (inter-subject factor) will be investigated by means of (repeated measures) analyses of variance ((rm)ANOVAs, parametric) or Mann-Whitney *U* tests / Friedman tests (non-parametric), and post hoc *t*-tests. Equivalence tests will also be used to investigate a comparable increase in the stress responses between the TSST conditions. For this purpose, mean or median values will be calculated from the variables for each group, depending on the distribution of the data and the test used. Area under the curve (AUC) values will also be calculated for analysis of changes in hormonal stress responses [53]. Possible associations between subjective sleep quality / quantity, mood, personality traits and hormonal awakening responses, diurnal profiles, and stress reactions will be analyzed by means of correlations and regression analyses. Again, parametric (e g., Pearson correlation) or non-parametric tests (Spearman or Kendall correlation) will be used depending on the normal distribution and scale level of the data. For multiple comparisons, the *p* values will be corrected according to the false discovery rate (FDR) [54]. Here, the primary outcome variables are corrected collectively across all parameters due to the underlying common hypothesis of a multimodal stress response to the TSST. The statistical significance level will be set to *α* = .05.

